#### Non-inclusion criteria

Participants who meet any of the following criteria will not be included: known diagnosis of crystal arthritis, autoimmune arthritis, hemochromatosis, or fibromyalgia; hand surgery in the past 6 months or scheduled in the next 6 months; intra-articular hyaluronic acid injection in the affected joint in the past 6 months; intra-articular steroid injection in the affected joint in the past month; significant injury to the affected joint in the past 6 months; any other self-reported hand condition that likely contributes to pain at the base of the thumb; poor general health likely to interfere with compliance or assessments, judged by the investigator; women who are pregnant or breastfeeding; or current use of any of the study interventions.

#### Exclusion criteria

Participants who undergo intra-articular injection of steroids or hyaluronic acid, begin physical or occupational therapy for thumb base OA, and suffer upper limb trauma or fracture requiring surgical intervention or not during the proposed 6-week treatment period will be excluded from the study.

### Who will provide informed consent? {26a}

All eligible participants will receive information about the study, and the blinded evaluator will obtain written informed consent (IC) from participants prior to assessment.

### Additional consent provisions for collection and use of participant data and biological specimens {26b}

Not applicable

### Interventions

#### Explanation for the choice of comparators {6b}

The intervention group will perform manual thumb joint mobility and 1st DI strengthening exercises. The control group will be submitted to a standard manual exercise protocol with proven benefits, previously published in the literature. All the sessions for both groups will be carried out in person, on non-consecutive days, with one of the two physiotherapists trained to apply the protocols.

The intervention will take place over a 6-week period, with three 45-min sessions a week, totaling 18 treatment sessions. The first session will take place 1 week after the baseline assessment. Both intervention protocols will be applied based on the shaping method for exercise load progression, as described below.

#### Intervention description {11a}

##### Control group

The control group will perform a manual exercise protocol with traditional exercises for CMC OA patients, based on the protocol of Gravas et al [18]. The hand mobility and stretching exercises will be executed in the order described in the protocol, with 10 repetitions each, throughout the treatment period.

The strength and joint stability exercise will also be performed as described, but the volume and load progression will be different. Progression parameters will also be used for the load. As such, for exercises 4, 5, and 6:
Volume: 10 repetitions of 15 s eachFeedback measurement parameter (FMP): number of repetitions performed in 15 sProgression parameter 1 (PP1): increase the resistance of the elastic (different color elastic) or the mass

It is important to emphasize that exercise 5 will be performed with a silicone grip ball in order to ensure optimal load progression.

The exercises will be applied in the order described in the original protocol.

##### Intervention group

The group focused on strengthening the 1st DI will perform 6 mobility and 6 strengthening exercises, divided into even and odd treatment days. The mobility exercises will be interspersed with the strengthening exercises to prevent muscle fatigue.

The following are the even treatment session:
Thumb opposition: touch the tip of each fingertip with the thumb.Volume: 10 repetitions2.Index finger abduction: palm and forearm flat on the table. The elastic will be placed around the PIP and fixed next to the 5th metacarpal. Perform index finger abduction by sliding it along the table.Volume: 10 repetitions of 15 s eachFeedback measurement parameter (FMP): number of repetitions performed in 15 sProgression parameter 1 (PP1): increase the fixing distance by 2 cmProgression parameter 2 (PP2): increase the resistance of the elastic (different color)3.Thumb abduction: start with the thumb lying flat against the palm, in line with the index finger. Move the thumb as far from the palm as possible, staying in line with the index finger.Volume: 10 repetitions4.Dragging Styrofoam balls: palm on the board and forearm on the table. The Styrofoam ball with Velcro should be positioned on the middle phalanx of the index finger. Perform index finger abduction to push the ball over the board, without lifting the finger off the table.Volume: 10 repetitionsFeedback measurement parameter (FMP): time taken (in seconds) to carry the ball from one end of the board to the otherProgression parameter 1 (PP1): tilt the boardProgression parameter 2 (PP2): place an elastic band around/on the PIP5.Thumb CMC extension: move the thumb as far as possible from the palm, without hyperextending the thumb MP joint.Volume: 10 repetitions6.Adduction and abduction of the index finger and thumb: the index finger and thumb semi-flexed and other fingers flexed. Perform adduction and abduction of the index finger and thumb to pick up wooden stars from within a 15-cm area.Volume: 10 repetitionsFeedback measurement parameter (FMP): time taken to pick up stars in a 15-cm areaProgression parameter 1 (PP1): increase the area to 30 cmProgression parameter 2 (PP2): increase the area to 45 cm

The following are the odd treatment session:
Thumb flexion: start with the thumb extended outward as far as possible from the palm. Flex the tip of the thumb to touch the base of the little finger.Volume: repeat 10 times2.Index finger abduction: start the exercise with the drawer positioned in the center of the patient, 0 cm from the edge of the table. Open the drawers from the bottom to top and right to left using the side edge of the index finger.Volume: 10 repetitions of 30 s eachFeedback measurement parameter (FMP): number of drawers opened in 30 sProgression parameter 1 (PP1): add elastic load behind each drawerProgression parameter 2 (PP2): increase the distance of all the elastics by 2 cm3.Thumb IP flexion: bend only the tip of the thumb (IP joint).Volume: 10 repetitions4.Aquarium net: start the exercise with the forearm in a neutral position supported on the backrest of the chair. The aquarium net will be placed in the patient’s hand, between the index finger and thumb. Perform abduction of the index finger, touching the lower edge of the table with the aquarium net.Volume: 10 repetitionsFeedback measurement parameter (FMP): time taken (in seconds) to touch the bottom edge of the table with the aquarium net 10 timesProgression parameter 1 (PP1): add 2 artificial ice cubes to the aquarium net5.Thumb MP flexion: bend only the MP joint.Volume: repeat 10 times.

#### Criteria for discontinuing or modifying the allocated interventions {11b}

Participants are free to withdraw from the study at any time and for any reason without penalty. Participants will be withdrawn from the study if they begin a different treatment in another location.

#### Strategies to improve adherence to interventions {11c}

In order to avoid and minimize missing data, all participants will receive paper reminders with the date and time of each session. The investigator will also contact them by phone to reinforce this schedule. In addition, patients will be asked to inform the physiotherapist responsible for the treatment of their pain level that week (according to the VAS) of any complications on a weekly basis.

#### Relevant concomitant care permitted or prohibited during the trial {11d}

During the intervention and follow-up, participants will be given a diary to document on which days of the week and for how many hours they used orthoses. They will also be advised not to seek any treatment after the end of the intervention, and should they do so, it must be reported in writing. No guidance or restrictions will be given on the use of analgesic drugs, but participants will be asked to record the name of the drug, as well as the date and dosage used.

#### Provisions for post-trial care {30}

All study patients will be entitled to follow-up treatment if pain worsens after the intervention. Any harm suffered by patients due to participation in the study will be remedied. For ethical reasons, the treatment that produces the best results will be offered to the other group at the end of the study.

### Outcomes {12}

#### Primary outcomes

The primary outcomes will be change in pain scores at the base of the thumb, assessed by VAS (0–100 mm), at rest and during pinch movement from baseline to 6 weeks [30]; change in hand function, evaluated using the Australian/Canadian Hand Osteoarthritis Index (AUSCAN) (0–36) from baseline to 6 weeks [30]; change in values of pinch strength (Lafayette Hydraulic Pinch Gauge (in kg)) from baseline to 6 weeks; and change in magnitude of activation of the abductor pollicis brevis (APB), 1st DI, extensor pollicis brevis (EPB), and abductor pollicis longus (APL) from baseline to 6 weeks.

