##### Physical assessment

All participants will be assessed for manual dexterity, hand function, grip and pinch strength, and muscle activation.

Manual dexterity will be evaluated using the NHPT, a wooden board with nine holes (3 rows × 3 columns) that must be filled with nine wooden pegs. The participant will be instructed to place the pegs into the holes one at a time in any order and then remove them and place them in the container next to the board. The test will be timed [35] and performed bilaterally, starting with the dominant upper limb.

Hand function will be assessed using the activities in the BULFT, which involves performing thirteen tasks. The positioning of the participant and the evaluator’s instructions on executing each task will be in line with the test administration manual. All tasks performed will be timed.

Maximum grip and pinch (pulp-pulp, lateral, and tripod) strength will be determined with a manual hydraulic dynamometer (Lafayette Professional Hand Dynamometer) and Lafayette hydraulic pinch gauge, respectively. The recommendations of the American Society of Hand Therapists (ASHT) will be followed and participants will perform three repetitions of 6 s each, with 1-min rest intervals [36]. The average of the three repetitions will be used for statistical analysis. The tests will be performed bilaterally, starting with the dominant upper limb.

The magnitude of muscle activation will be measured during the grip and pinch strength tests, using a Trigno Wireless System (Delsys Inc., Boston, USA) at a sampling frequency of 1200 Hz and three Trigno mini wireless sensors (Trigno EMG sensor, Delsys Inc., Boston, MA), with a rejection rate higher than 80 dB. To evaluate the thumb APB, the mini electrode will be placed in the center of the thenar eminence, in the same direction as the thumb. For 1st DI assessment, the mini electrode will be placed on the dorsal surface of the hand, in the space between the index finger and thumb, while the participant performs the pinch movement. To evaluate EPB and APL, the mini electrode will be placed in the dorsal region of the forearm above the wrist and on the same side as the thumb, while the participant abducts the thumb [37]. Before positioning the electrodes, the skin in the area will be prepared as recommended by Surface Electromyography for the Non-Invasive Assessment of Muscles (SENIAM) [38].

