## Statistical methods

### Statistical methods for primary and secondary outcomes {20a}

Data will be analyzed according to the intention-to-treat principle. All trial outcomes will be blinded for treatment allocation, and all participants will be analyzed in the treatment group to which they were originally randomized. Statistical analysis will be performed using the Statistical Package for the Social Sciences, version 19.0 (SPSS Inc., Chicago, IL, USA). A 5% significance level will be adopted for all analyses. The normality of the residues will be verified by the Shapiro-Wilk test. Pain, function, activity and participation, grip and pinch strength, dexterity, and muscle activation will be compared between the groups (control and intervention) and stages (pretreatment, 4- and 6-week assessments, follow-up), and interactions between them analyzed by mixed model ANOVA considering group and time factors for repeated measures if the residuals exhibit normality with post hoc contrasts (treated versus control group).

The first statistical procedure will be to verify, in general and at each assessment stage (pretreatment, 13th and 18th assessment, follow-up) if pain, function, activity and participation, grip and pinch strength, dexterity, and muscle activation differ between the intervention and control groups. The second statistical procedure aims to verify whether pain, function, activity and participation, grip and pinch strength, dexterity, and muscle activation change over the four assessment stages (pretreatment, 4- and 6-week assessments, follow-up) within each group.

The quantitative variables will be expressed as minimum and maximum values, means, medians, standard deviations, coefficients of variation, and asymmetry coefficients. Categorical variables will be expressed as frequencies and percentages.

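### Eight primary outcomes at 6 weeks, 5% stated for every analysis and no success rule: the chance of a false positive primary result is about 12% to 34%, not 5%

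*Protocol article*

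**What the plan says.** All references are to the protocol article.

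- **Primary outcomes.** The list opens "The primary outcomes will be change in pain scores at the base of the thumb", with pain taken "at rest and during pinch movement from baseline to 6 weeks". It adds AUSCAN hand function, pinch strength and "change in magnitude of activation of the abductor pollicis brevis (APB), 1st DI, extensor pollicis brevis (EPB), and abductor pollicis longus (APL) from baseline", all to 6 weeks. That is 2 + 1 + 1 + 4 = 8 named variables.
- **Secondary outcomes.** The 4-week and 18-week changes in these same variables are secondary.
- **Objectives {7}.** The main objective covers pain, strength and function. Muscle activation appears only among the secondary objectives.
- **Statistical methods {20a}.** "A 5% significance level will be adopted for all analyses". No adjustment, ranking or success rule is given.
- **Sample size {14}.** Effect size 0.25, 5% significance and 90% power give 46 participants, raised to 56 for losses. One calculation serves pain, dexterity, function, strength and activation.
- **Physical assessment.** "Maximum grip and pinch (pulp-pulp, lateral, and tripod) strength will be determined", so pinch strength has three forms. Activation is recorded during both the grip and the pinch tests. The equipment is "three Trigno mini wireless sensors", and "To evaluate EPB and APL, the mini electrode will be placed in the dorsal region of the forearm", a single site for the two muscles.

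**The concern.** With eight primary outcomes of equal standing, a reader cannot tell in advance which result will decide the trial. If each is compared with 5%, one significant result among eight could be reported as the primary finding when the two protocols do not differ.

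This matters because the Discussion promises a conclusion on superiority, and Provisions for post-trial care {30} says that the treatment with the better results will be offered to the other group. Neither section says which outcome settles the matter.

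The primary set is also loose in two places. Pinch strength could mean any of three measurements, and activation could be taken from the grip test or from a pinch test. The document further disagrees with itself on whether activation is primary.

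**Working it through.** **The plan's own figure.** I take the effect size of 0.25 as Cohen's f, with two groups. The correlation between repeated measures and the effect tested are not stated, so both are assumptions here. With N participants, m stages and correlation ρ, the noncentrality is:

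- group-by-time interaction: λ = f²·N·m/(1−ρ), with (m−1) and (N−2)(m−1) degrees of freedom
- between groups: λ = f²·N·m/(1+(m−1)ρ), with 1 and N−2 degrees of freedom

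Three variants give exactly 46 at 5%:

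- interaction, m = 4, ρ = 0.22: λ = 0.0625×46×4/0.78 = 14.7, power 90.3%
- interaction, m = 2, ρ = 0.5: λ = 0.0625×46×2/0.5 = 11.5, power 91.2%
- between groups, m = 4, ρ = 0: λ = 0.0625×46×4/1 = 11.5, power 91.2%

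With m = 4 and ρ = 0.5 the answer would be 30 (interaction) or 108 (between groups). So 46 is attainable but cannot be confirmed. The step to 56 reproduces: 46×1.2 = 55.2, rounded up to an even number. Every variant uses one test at 5%.

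**False positive rate.** For k independent tests at 5%, the chance of at least one false positive is 1 − 0.95^k.

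| Way of counting the primary set | k | Independent |
|---|---|---|
| Without activation | 4 | 18.5% |
| One pinch value, three muscle signals | 7 | 30.2% |
| As named | 8 | 33.7% |
| Three pinch types, three muscle signals | 9 | 37.0% |

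The outcomes are probably correlated, but the article gives no correlations. For k = 8, two-sided tests and an assumed common correlation, simulation (400,000 draws of equicorrelated normal statistics) gives:

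| Correlation | 0.3 | 0.5 | 0.7 | 0.9 |
|---|---|---|---|---|
| At least one false positive | 29.9% | 24.9% | 19.0% | 11.9% |

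Counting only false positives that favour the intervention, eight independent tests give 1 − 0.975^8 = 18.3%, against 2.5% for one test.

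**Cost of keeping all eight.** Holm compares the smallest p-value with 0.05/8 = 0.00625, so Bonferroni at that level is the conservative guide. The family-wise error becomes 1 − (1−0.00625)^8 = 4.9% if independent. Under the three variants that reproduce 46, 90% power then needs 68 to 70 evaluable participants, and power per outcome is about 70% at 46 and 81% to 82% at 56. If the interaction is tested over four stages with ρ = 0.5, 44 are enough and power at 46 is 92%. The cost therefore turns on the unstated correlation.

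**Muscles against signals.** The outcome lists name APB, 1st DI, EPB and APL. Physical assessment describes three sensors: one for APB, one for 1st DI, and one site for EPB and APL together. Four named outcomes therefore rest on three signals.

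**The case against.** The strongest reply is that a 5% level need not mean 5% per test. Adjusted p-values are also compared with 5%, the article mentions post hoc contrasts without giving their method, and a separate analysis plan may supply the adjustment. This stands in part: a reader might infer that the article excludes any adjustment, and it does not. It only states none. But the choice of primary outcome belongs in the protocol, and here eight are named without a rule.

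A second reply is that the main objective joins pain, strength and function, which could mean that all must improve. Under such a rule there would be no inflation. The wording is not framed as a success rule, though, and it leaves out activation, which the outcome list makes primary.

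Three stronger readings are tempting, and the documents do not support them:

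- **That a false positive is more likely than not.** Eight tests give 34% or less. Passing 50% takes 14 independent tests. One can reach 22 by counting three pinch types and four muscles over four tasks (2 + 1 + 3 + 16; 1 − 0.95^22 = 68%), but the article does not make each task a primary outcome, and four muscle signals do not exist.
- **That comparisons at each stage multiply the primary error.** The primary outcomes are fixed at 6 weeks, the 4-week and 18-week changes are secondary, and a pretreatment comparison cannot support an efficacy claim.
- **That the sensor mismatch adds to the error.** Fewer distinct signals mean fewer tests. It is a fault of definition, to be handled on its own.

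**Conclusion.** The concern holds for the eight outcomes as named. Followed as written, the plan carries a chance of about 12% to 34% of at least one false positive primary result, for assumed common correlations from 0.9 down to 0, against a nominal 5%. This assumes that each outcome is tested once at 6 weeks, two-sided, at an unadjusted 5%. Treating EPB and APL as one signal gives seven outcomes and 30% if independent, so the conclusion does not depend on the exact count.

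Two further faults in the primary set are matters of text, not of arithmetic: the primary pinch type is not specified, and activation is primary in one section and only a secondary objective in another. The mismatch of four muscles and three signals is also established, as a separate point. Because the first fault bears on the trial's headline conclusion, it should be corrected before any comparison between groups is seen.

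**What to change.** 1. Preferred: name one primary outcome at 6 weeks, tested at 5%, and make the others secondary. The choice is the sponsor's, from the pain, strength and function of the main objective.
2. Alternative: keep a short listed family, specify the pinch type (and the EMG task, if activation stays in it), test it with Holm at an overall 5%, and restate the power per outcome with the assumed correlation and the tested effect.
3. Move muscle activation to secondary, so that the outcome list agrees with the objectives.
4. Separately, redefine activation in both the primary and the secondary lists as three signals: APB, 1st DI and combined EPB/APL.

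The cost is a change of wording, notified to the ethics committee, the journal and the registry as the article already provides. Under option 1 the other outcomes lose primary status. Under option 2 power per outcome falls or the sample grows; the figures above for eight outcomes are the upper end, and a shorter family costs less.

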#### Secondary outcomes

The secondary outcomes will be change in VAS pain scores (0–100 mm) at the base of the thumb, at rest and during pinch movement from baseline to 4 and 18 weeks; change in hand function, assessed by the AUSCAN function section (0–36) from baseline to 4 and 18 weeks; change in social participation according to the Canadian Occupational Performance Measure (COPM) tool from baseline to 4, 6, and 18 weeks, change in pain based on the AUSCAN pain section (0–20) from baseline to 4, 6, and 18 weeks; change in manual dexterity as per the Nine-Hole Peg Test (NHPT) (expressed in seconds) from baseline to 4, 6, and 18 weeks; change in values of grip strength from baseline to 4, 6, and 18 weeks (Lafayette Professional Hand Dynamometer (in kg)) and pinch strength (Lafayette Hydraulic Pinch Gauge (in kg)) from baseline to 4 and 18 weeks; change in execution time (expressed in seconds) of Bilateral Upper Limb Function Test (BULFT) tasks from baseline to 4, 6, and 18 weeks; and magnitude of activation of the abductor pollicis brevis (APB), 1st DI, extensor pollicis brevis (EPB), and abductor pollicis longus (APL) from baseline to 4 and 18 weeks.

### Participant timeline {13}

Table 1 shows which evaluations will be performed on patients throughout the study period, i.e., in pre-treatment, during each session, and at follow-up.

**Table 1 Tab1:** Participant timeline

	Pretreatment	1st	2nd	3rd	4th	5th	6th	7th	8th	9th	10th	12th	13th	14th	15th	16th	17th	18th	Follow-up
Evaluation form	X																	X	X
Pain	X												X					X	X
AUSCAN	X												X					X	X
COPM	X												X					X	X
NHPT	X												X					X	X
BULFT	X																	X	X
Grip strength	X																	X	X
Pinch strength	X																	X	X
Muscle activation	X																	X	X

*AUSCAN* Australian/Canadian Hand Osteoarthritis Index, *COPM* Canadian Occupational Performance Measure, *NHPT* Nine-Hole Peg Test, *BULFT* Bilateral Upper Limb Function Test

